PwMS will be included at baseline irrespective of whether they have depression at study entry, or long-term depression, or depression already managed with pharmacotherapy or therapies. This is because of studies suggesting that PwMS scoring high on depression levels often have not been previously identified as having depression or anxiety within a cohort [28], and that even those with previously identified depression or anxiety are often undertreated [45]. Baseline testing will be done for all participants; therefore, participants will become their own controls, as to outcomes on change in levels of depression and anxiety over 3 months, and then 6 months in addition to other quality of life outcomes. Therefore, we will see if the NP involvement and the consequent additional supports, counseling, etc., provides a change over time from baseline depression and anxiety levels. We postulate that depression and anxiety may be most responsive to the holistic approach of an NP over the short term in comparison with other quality of life measures [30, 47]. The primary outcome of depression and anxiety score changes at 3 months was chosen as the primary outcome due to published studies examining efficacy of interventions for depression and anxiety for PwMS carrying out active intervention strategies ranging in duration from 6 to 16 weeks (median 12 weeks), demonstrating overall efficacy in mainly depression and suggested efficacy in anxiety by a systematic review and meta-analysis [47].

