A longer-term follow-up will be conducted at 12 months to evaluate the long-term differences of the 6-month intervention in change of the patient-reported outcome measures (HADS, MFIS, EQ5D, and CAREQOL-MS). By then, all participants would have seen the NP, and the goal of the late follow-up would be to see if there was (1) long-term impact of the 6-month NP intervention (from those in the original intervention group), and (2) to check the larger patient number impact of the NP intervention upon those within the control group.

If participants score very low or severe on their scales around anxiety, depression, fatigue, quality of life, and/or their caregivers score as very low on their questionnaire, their community neurologist and/or family physician will be contacted to see the participant on an urgent basis.

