### Sample size and power analysis

Honarmand and Feinstein (2009) [74], validated the use of HADS in PwMS [Baseline scores and standard deviation (SD)]. Using the validation information in the study by Honarmand and Feinstein and the following assumptions of 80% power and a two-sided alpha of 0.05, a total sample size of 200 (100 in each group) will be required to detect 1.5 difference [86], between the intervention and the control groups. The same size has been calculated for both HADS-A and HADS-D. This study will use the sample size calculated for HADS-A, as it required a larger sample size and to ensure there will be sufficient power for both HADS-A and HADS-D. This sample size will be inflated to 220 to account for possible dropouts, losses to follow-up, and withdrawals of consent.

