### Statistical analysis

Data analysis will be performed using the computer R 3.4.0 software (Vienna, Austria; https://www.R-project.org/) and SAS 9.4 software (SAS Institute Inc. Cary, NC, USA). Patient demographic and clinical characteristics will be analysed using descriptive statistics.

The primary outcome of difference in change of HADS-D and HADS-A from baseline to 3 months between the intervention and control, will be tested using an independent *T*-test. The last observation will be carried forward in the case of missing data. Secondary outcomes will be analysed using the same methods as described below. The CSQ will be treated as continuous variables with an overall satisfaction score as a sum of the sub-scales for each question in the CSQ.

Categorical variables will be reported using frequency and percentage and continuous variables will be reported using mean (SD) or median [interquartile range (IQR)] as appropriate. Univariable analysis will be conducted to determine if there is a statistical significance between the outcomes (e.g. baseline to 3 months and 6 months, respectively). Chi-square and independent *T*-tests will be used for the univariate analysis, or where appropriate the non-parametric tests (Fishers test and Wilcoxon rank test). ANOVA and generalized linear models will be used to test for overall differences between the intervention and control at the different timepoints and variances amongst the variables by group and timepoints. Post hoc Tukey HSD (Honestly Significant Difference) test will be performed afterwards with adjustments made using the Bonferroni method. All test assumptions will be checked during the data analysis process. Statistical significance will be set at *p* values less than 0.05. In the case of missing data, we will utilize the last value carried forward method to impute missing values.

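### The own-controls rationale and the second 12-month goal read an uncontrolled before-after change as the nurse practitioner's effect

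*Protocol article*

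**What the plan says.** Three places in the Protocol article bear on this.

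- **Population (inclusion/exclusion criteria).** Having explained that people enter whatever their depression status, the text says that, because baseline is measured, "participants will become their own controls" for change over 3 and then 6 months. It concludes that the study will therefore see whether NP involvement, with the support that follows from it, "provides a change over time from baseline depression and anxiety levels".
- **Outcomes, 12-month follow-up.** The text states that every participant will have had NP contact by then. It gives two goals: the lasting impact of the 6-month intervention in the original intervention group, and "to check the larger patient number impact of the NP intervention upon those within the control group".
- **Statistical analysis.** Univariable analysis is to "determine if there is a statistical significance between the outcomes (e.g. baseline to 3 months and 6 months, respectively"). The next sentence names chi-square and independent t-tests, with non-parametric alternatives.

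Elsewhere the plan is comparative. Outcomes and Statistical analysis define the primary outcome as the between-arm difference in HADS change at 3 months. Outcomes frames the secondary questionnaire outcomes at 3 and 6 months as differences in change, to be compared between arms. Validity and reliability gives the 12-month follow-up a further aim: whether the timing of NP access matters in the long term.

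**The concern.** A change from baseline within one group answers whether scores moved. It does not answer whether the NP moved them. In one group, observed change = NP effect + everything else that moves scores over the same interval. The document itself supplies candidates for the second term:

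- Patients are referred because someone thinks they may benefit, so some may enter at a bad moment (Population).
- Neurologist and family-physician care continues in both arms (Control arm).
- Severe scores in either arm prompt urgent physician contact (Outcomes).
- On the latest dates in Trial status, the last 6-month visits fall in November 2020 and the 12-month questionnaires in spring 2021, so calendar effects are possible.

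Up to 6 months the randomised control arm experiences the same background and subtracts it. At 12 months no untreated arm is left, so the NP's impact on the former controls can come only from their own change over time or from pooling both arms' NP periods. The reference to a larger patient number suggests pooling. Neither is a randomised contrast.

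Results are to go to the health service when it considers continued funding of the post (Dissemination). Improvement that would have happened anyway could be credited to the NP. Worsening could equally hide a benefit: a true effect of -1.5 points with a drift of +1.0 shows as only -0.5.

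**Working it through.** **The plan's own figure.** Sample size and power analysis assumes "80% power and a two-sided alpha of 0.05" and states that "a total sample size of 200 (100 in each group) will be required to detect 1.5 difference". It gives no SD, so 200 cannot be reproduced from stated inputs. Solving backwards:

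SD = 1.5 / [(1.960 + 0.842) × √(2/100)] = 1.5 / 0.396 ≈ 3.79

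SDs from 3.75 to 3.80 give totals of 198 to 202, which is consistent with the plan. The SD of 3.79 used below is therefore an assumption.

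**Inputs for the illustration.** All are assumptions except the group size of 100.
- True NP effect: zero.
- Drift d: common to all patients; 0.25, 0.5 or 1.0 points. The document gives no drift figure.
- Correlation ρ between the two measurements: 0.5, with 0.7 for range.
- n = 100 (one arm) or 200 (both arms pooled).

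**Formulas.** SD of change = 3.79 × √[2(1 − ρ)], which is 3.79 at ρ = 0.5 and 2.93 at ρ = 0.7. The non-centrality of the before-after t-test is d / (SD of change / √n). At ρ = 0.5, n = 100 and d = 0.5 it is 0.5 / 0.379 = 1.32. The rejection probability comes from the non-central t distribution, two-sided 0.05.

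| Before-after test, no NP effect | d = 0 | d = 0.25 | d = 0.5 | d = 1.0 |
|---|---|---|---|---|
| n = 100, ρ = 0.5 | 5% | 10% | 26% | 74% |
| n = 100, ρ = 0.7 | 5% | 13.5% | 39% | 92% |
| n = 200, ρ = 0.5 | 5% | 15% | 46% | 96% |

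**Check by simulation** (20,000 trials per setting, ρ = 0.5). The one-arm before-after test rejected in 5.3%, 25.8% and 74.2% of trials at drifts of 0, 0.5 and 1.0, in agreement with the formula. On the same data the between-arm test of change rejected in 5.2%, 4.8% and 4.7%, because the shared drift cancels.

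For scale, 0.25 points is one sixth of the 1.5-point target (0.25 / 1.5), and 0.5 is one third.

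**The case against.** The strongest reply is that the planned inference is between arms. The primary outcome is a between-arm difference tested by an independent t-test, the 3- and 6-month secondary outcomes are compared between arms, and ANOVA and generalised linear models address intervention versus control at each time point. **This stands.** A reader might infer from the own-controls sentence that the main results rest on before-after change. The sections that govern the analysis do not support that.

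Secondly, a reader might take the baseline-to-3-and-6-months sentence in Statistical analysis as a plan for within-arm tests. It is followed by independent-sample tests, and the interval may simply name the change score on which the arms are compared. No paired test, and no 6-to-12-month test, is named anywhere. **This also stands:** the sentence is ambiguous and is not evidence of a within-arm test.

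Thirdly, the rejection rates follow from chosen inputs. Any test of zero change rejects when change is not zero. There is no HADS entry threshold, so the amount of regression to the mean is uncertain. The calendar argument depends on dates that the article gives inconsistently: Recruitment has enrolment complete in March 2019, while Trial status gives both November 2019 and May 2020. **Accepted:** the figures are an illustration.

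Lastly, the second 12-month goal has no specified test, and an analysis plan may supply one. **This does not rescue it.** A later document can choose a test, but it cannot create an untreated comparator at 12 months. The fault lies in the stated inference, not in a missing detail.

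**Conclusion.** The point holds within a limited scope. The own-controls reasoning in Population and the second 12-month goal in Outcomes both attribute an uncontrolled change to the NP, and at 12 months no concurrent untreated group exists to separate the two. The primary outcome and the between-arm contrasts at 3 and 6 months are untouched.

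The logical fault needs no numbers. Its size depends on assumed drift, an assumed correlation and a back-solved SD. Across the values shown, a before-after test on 100 patients with no NP effect would be significant in 10% to 13.5% of trials at 0.25 points of drift, 26% to 39% at 0.5 and 74% to 92% at 1.0. These are not error rates of any test that the protocol names, and should not be quoted as such. The wording should be corrected. It does not threaten the trial's main conclusion.

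**What to change.** - **Population.** Replace the own-controls inference with a statement that NP effects are judged by the randomised between-arm difference in change at 3 and 6 months.
- **Statistical analysis.** Make clear that the 3- and 6-month tests compare the arms.
- **Outcomes, second 12-month goal.** Recast it as a descriptive, non-randomised summary of the former control arm's change: mean with confidence interval, no p-value, no effect claim, and no pooling with the randomised estimate.
- **12-month between-arm comparison.** Keep it, described as early versus delayed NP access, in line with the timing aim in Validity and reliability.

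One tempting repair should not be adopted as an estimate of NP effect: the controls' 6-to-12-month change minus their 0-to-6-month change. It removes only linear drift. If controls fell by 1 point over the first 6 months through regression to the mean and then stayed level, with no NP effect, it would give 0 − (−1) = +1 and falsely suggest harm. Under equal correlations its variance is 6σ²(1 − ρ) against 2σ²(1 − ρ) for a simple change, three times as large.

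The cost is wording only; no new data are needed. The small downside is that the second 12-month goal no longer supports a causal statement.

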### Sample size and power analysis

Honarmand and Feinstein (2009) [74], validated the use of HADS in PwMS [Baseline scores and standard deviation (SD)]. Using the validation information in the study by Honarmand and Feinstein and the following assumptions of 80% power and a two-sided alpha of 0.05, a total sample size of 200 (100 in each group) will be required to detect 1.5 difference [86], between the intervention and the control groups. The same size has been calculated for both HADS-A and HADS-D. This study will use the sample size calculated for HADS-A, as it required a larger sample size and to ensure there will be sufficient power for both HADS-A and HADS-D. This sample size will be inflated to 220 to account for possible dropouts, losses to follow-up, and withdrawals of consent.

### Feasibility

We investigated the feasibility of this intervention by searching community neurologists’ electronic medical record databases to identify the number of PwMS typically followed by each of the seven neurologists. The number of PwMS in these practices does fluctuate over time (movement of PwMS in and out of the province, referral to another neurologist, or loss to follow-up, etc.). There were greater than 2000 PwMS followed by community neurologists as of January 2017. There is also an established NP practice in the tertiary MS clinic at the University of Alberta, seeing more than 400 PwMS per year. Thus, we have determined that we will be able to recruit the required 200 PwMS for the study. The iPad has been piloted in the community neurologists’ offices, found to be easy to use by PwMS. There is no interpretation of the iPad EQ5D other than the patient’s interpretation of the EQ5D results, and the prompt to discuss their results with their neurologist. For those PwMS who do not wish to feel pressured to complete the iPad registration in the waiting room, they will have also been given a flyer. Then, when they arrive home, they can link into the study information sheet and consequent consent at their choice and leisure.

### Preliminary screening

Prior to conducting statistical analysis, preliminary screening will be conducted using SAS 9.4 software (SAS Institute Inc., Cary, NC, USA) to ensure that all the enrolled patients meet the eligibility inclusion and exclusion criteria and confirm the participants provide informed consent.

### Statistical analysis

Data analysis will be performed using the computer R 3.4.0 software (Vienna, Austria; https://www.R-project.org/) and SAS 9.4 software (SAS Institute Inc. Cary, NC, USA). Patient demographic and clinical characteristics will be analysed using descriptive statistics.

The primary outcome of difference in change of HADS-D and HADS-A from baseline to 3 months between the intervention and control, will be tested using an independent *T*-test. The last observation will be carried forward in the case of missing data. Secondary outcomes will be analysed using the same methods as described below. The CSQ will be treated as continuous variables with an overall satisfaction score as a sum of the sub-scales for each question in the CSQ.

Categorical variables will be reported using frequency and percentage and continuous variables will be reported using mean (SD) or median [interquartile range (IQR)] as appropriate. Univariable analysis will be conducted to determine if there is a statistical significance between the outcomes (e.g. baseline to 3 months and 6 months, respectively). Chi-square and independent *T*-tests will be used for the univariate analysis, or where appropriate the non-parametric tests (Fishers test and Wilcoxon rank test). ANOVA and generalized linear models will be used to test for overall differences between the intervention and control at the different timepoints and variances amongst the variables by group and timepoints. Post hoc Tukey HSD (Honestly Significant Difference) test will be performed afterwards with adjustments made using the Bonferroni method. All test assumptions will be checked during the data analysis process. Statistical significance will be set at *p* values less than 0.05. In the case of missing data, we will utilize the last value carried forward method to impute missing values.

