### Randomization, allocation, and blinding

This is an interventional study with parallel groups, done through block randomization (variable block sizes) 1:1, using centralized secure website to (1) intervention group (NP-led care) and (2) control group (usual care—community neurologist/family physician and registered nurse (RN), in a non-inferiority framework). The EPICORE Centre will randomize and allocate consented patients who meet eligibility inclusion and exclusion criteria on a 1:1 ratio using a centralized secure website. Block randomization (using variable block sizes) will be used to ensure there are equal participants in the intervention and control arms and to further conceal allocation. The randomization sequence was generated using R blockrand (https://cran.r-project.org/package = blockrand) and the randomization function of REDCap (REDCap Consortium, Vanderbuilt University, Nashville, TN, USA). Participants will be enrolled into the study by the community neurologist’s office (e.g. registered nurse, NP, or neurologist). Participants will register themselves through filling out an iPad questionnaire in the waiting room of community neurologists’ offices, indicating whether they wish to participate in the study or not. The participants, after providing informed consent, will be randomized by the independent EPICORE Centre’s research team to either the intervention group of NP-led care or the control group of standard care provided by community neurologist and registered nurse. After participants have provided informed consent, the EPICORE Centre’s research team will use a centralized website to randomize the patients to either the intervention or control group and then the NP and/or community neurologist will provide the intervention. Participants will be randomized to either the intervention group of NP-led care or the control group of standard care provided by community neurologist and registered nurse. Due to the nature of the intervention, blinding of the providers or patients will not be possible. However, the statistician will be blinded as to which group represents the intervention and control.

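### The primary t-test on 3-month change in HADS ignores baseline as a covariate and so loses precision; if the trial was sized from a single-timepoint SD, its 80% power needs a baseline-to-3-month correlation of about 0.5 or more

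*Protocol article*

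**What the plan says.** The Outcomes section defines the primary outcome as the between-group difference in change in HADS-D and HADS-A at 3 months. The Statistical analysis section fixes the test: the "difference in change of HADS-D and HADS-A from baseline to 3 months between the intervention and control, will be tested using an independent" t-test, with the last observation carried forward for missing values. The same section later names ANOVA and generalized linear models, but for overall differences across timepoints. It does not assign them to the primary comparison and does not name baseline HADS as a covariate.

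The Sample size and power analysis section says that a cited study "validated the use of HADS in PwMS [Baseline scores and standard deviation (SD" and then, under "assumptions of 80% power and a two-sided alpha of 0.05", that "a total sample size of 200 (100 in each group) will be required to detect 1.5 difference". HADS-A drives the number: "This study will use the sample size calculated for HADS-A, as it required a larger sample size". Enrolment is then raised: "This sample size will be inflated to 220 to account for possible dropouts, losses to follow-up, and withdrawals of consent". The section prints no numeric SD, no SD of change and no correlation between baseline and 3 months.

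**The concern.** There are two linked issues.

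**Precision.** Every participant is to complete HADS at baseline, so the baseline score is available at no extra cost. Subtracting it is one way to use it; fitting it as a covariate is another, and the second is at least as precise. The plan fixes the less precise option for its main comparison.

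**Match between sizing and test.** The variance of a change score depends on the baseline-to-follow-up correlation. If 100 per arm was solved from the spread of HADS at one time, the quoted 80% is the power of a comparison of single-timepoint scores, not of the planned test on change. The two agree exactly at only one correlation. Below it the planned test has less than 80% power, and above it more.

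Recruitment is complete according to the Trial status section, so the number of participants can no longer respond. The analysis model is what remains open to improvement.

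**Working it through.** **Inputs from the protocol article.** 100 per arm; difference 1.5; two-sided alpha 0.05; power 80%; 1:1 allocation.

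**Assumptions, not in the document.** The sample size was solved with a single-timepoint SD; variances are equal at baseline and 3 months; the correlation rho is unknown and is shown as a range.

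**Step 1: the plan's own figure.** N = 200 cannot be reproduced forwards because no SD is printed. Solving backwards (normal approximation):

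SD = 1.5 / (1.960 + 0.842) × sqrt(100/2) = 3.79 (3.77 with the noncentral t).

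An SD of 3.78 returns 100 per arm. The value is implied, not documented.

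**Step 2: SD of the analysed quantity.**

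- t-test on change: SD × sqrt(2(1 − rho))
- 3-month score adjusted for baseline: SD × sqrt(1 − rho²)
- Ratio of variances, adjusted to change: (1 − rho²) / (2(1 − rho)) = (1 + rho)/2

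The first equals the single-timepoint SD when 2(1 − rho) = 1, that is, at rho = 0.5.

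**Step 3: power at 100 per arm.** By construction, 1.5 divided by its standard error is 2.802 with the single-timepoint SD. Power is therefore Φ(2.802/sqrt(2(1 − rho)) − 1.960) for change and Φ(2.802/sqrt(1 − rho²) − 1.960) for the adjusted model. The SD cancels, so these results do not depend on its unprinted value. For example, at rho 0.4: 2.802/sqrt(1.2) − 1.960 = 0.598, giving 72%.

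| rho | SD of change | Power, change | Total N for 80% | Adjusted SD | Power, adjusted | Total N for 80% | Variance ratio |
|---|---|---|---|---|---|---|---|
| 0.3 | 4.48 | 66% | 280 | 3.61 | 84% | 182 | 0.65 |
| 0.4 | 4.15 | 72% | 240 | 3.47 | 86% | 168 | 0.70 |
| 0.5 | 3.79 | 80% | 200 | 3.28 | 90% | 150 | 0.75 |
| 0.6 | 3.39 | 88% | 160 | 3.03 | 94% | 128 | 0.80 |
| 0.7 | 2.93 | 95% | 120 | 2.70 | 97.5% | 102 | 0.85 |

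At rho = 0 the adjusted model has 80% power and the t-test on change 51%.

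**Step 4: effect of the inflation to 220.** 1 − 200/220 = 9.1%, so 220 allows for about 9% loss. If all 110 per arm were analysed with no dilution of the effect, the t-test on change would have 70% power at rho 0.3, 76.5% at 0.4 and 84% at 0.5. Break-even is where 2(1 − rho) = 110/100, so rho = 0.45.

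**The case against.** **The baseline-SD reading is an inference.** The bracketed words describe what the cited study supplies, and the next sentence says only "Using the validation information in the study by" that source. The planners may have converted a baseline SD into an SD of change with an assumed correlation, and an article condenses such detail. This stands. The power figures are conditional on that reading; the precision argument is not.

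**The t-test on change is a legitimate analysis.** It matches the declared outcome. Under randomization it is unbiased and controls the type I error. A reader might infer that regression to the mean after a chance baseline imbalance makes it invalid. The documents do not support that: such imbalance affects a single realised result, and the test's standard error already allows for it. The cost is precision.

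**The trial may be adequately powered.** A reader might also infer that the 80% is right only at a correlation of 0.5, or that the trial is underpowered. Exactly 80% does occur only there, but any higher correlation gives more, and the document supplies no correlation from which to show a shortfall. The inflation to 220 could lower the threshold to 0.45 if nobody were lost. Carrying baseline values forward could keep participants in the analysis but may dilute the effect, so this is only a partial rescue.

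**The change would be late.** Trial status reports recruitment complete and 6-month visits finished. Data monitoring plans an interim analysis after the 3-month follow-up, which is the primary timepoint. Replacing the primary test after seeing results by arm would be a problem of its own. This stands as a condition on the fix. It does not defend the unadjusted test.

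**Conclusion.** The point holds as one of efficiency and of an incompletely stated sample size, not of validity. The plan fixes an unadjusted test on change for its primary comparison. With equal variances, adjusting for baseline reduces the variance at every correlation below 1, apart from a trivial loss of one degree of freedom: by 25% at rho 0.5 and by 20% at rho 0.6.

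If 100 per arm was solved from a single-timepoint SD, the t-test on change reaches 80% power only when rho is about 0.5 or more. The baseline-adjusted model holds about 80% or more at any rho of 0 or above. Both statements also assume that the SD taken from the external study applies to this trial's population. The figures refer to HADS-A, which the plan says needs the larger sample.

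**What to change.** 1. In Statistical analysis, make the primary analysis a linear model of 3-month HADS-A, and likewise HADS-D, on arm and baseline score. Report the adjusted difference with its 95% confidence interval. Keep the t-test on change as a supportive analysis.
2. Record this as a dated amendment made before any unblinded primary analysis. State whether the interim analysis after the 3-month follow-up has been run and whether anyone has seen results by arm. If the primary comparison has already been seen, the change can no longer count as prespecified, and the adjusted result should be labelled accordingly.
3. In Sample size and power analysis, print the SD used and say whether it is a single-timepoint SD or an SD of change. If it is single-timepoint, say that the 80% refers to the unadjusted score and is conservative for the adjusted analysis. If it is an SD of change, give the correlation assumed.

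No new data are needed, because baseline HADS is already collected. The cost is the amendment, the wording and the confirmation of blinding. The sample size does not change.
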